## Abstract

**Background:**

Fewer than one in ten out-of-hospital cardiac arrest (OHCA) patients survive to hospital discharge in the UK. For prehospital teams to improve outcomes in patients who remain in refractory OHCA despite advanced life support (ALS); novel strategies that increase the likelihood of return of spontaneous circulation, whilst preserving cerebral circulation, should be investigated. Resuscitative Endovascular Balloon Occlusion of the Aorta (REBOA) has been shown to improve coronary and cerebral perfusion during cardiopulmonary resuscitation. Early, prehospital initiation of REBOA may improve outcomes in patients who do not respond to standard ALS. However, there are significant clinical, technical, and logistical challenges with rapidly delivering prehospital REBOA in OHCA; and the feasibility of delivering this intervention in the UK urban–rural setting has not been evaluated.

**Methods:**

The Emergency Resuscitative Endovascular Balloon Occlusion of the Aorta in Out-of-Hospital Cardiac Arrest (ERICA-ARREST) study is a prospective, single-arm, interventional feasibility study. The trial will enrol 20 adult patients with non-traumatic OHCA. The primary objective is to assess the feasibility of performing Zone I (supra-coeliac) aortic occlusion in patients who remain in OHCA despite standard ALS in the UK prehospital setting. The trial’s secondary objectives are to describe the hemodynamic and physiological responses to aortic occlusion; to report key time intervals; and to document adverse events when performing REBOA in this context.

**Discussion:**

Using compressed geography, and targeted dispatch, alongside a well-established femoral arterial access programme, the ERICA-ARREST study will assess the feasibility of deploying REBOA in OHCA in a mixed UK urban and rural setting.

Trial registration.

ClinicalTrials.gov (NCT06071910), registration date October 10, 2023, https://classic.clinicaltrials.gov/ct2/show/NCT06071910

## Background

Resuscitation is attempted by prehospital emergency medical services (EMS) in approximately 30,000 out-of-hospital cardiac arrest (OHCA) patients each year in the UK. However, fewer than one in ten patients (9%) survive to hospital discharge.^1^ This is significantly lower than several other countries with developed EMS systems, that report survival rates of up to 18%.^1^, ^2^ Therefore, there is considerable potential to improve outcomes from OHCA in the UK.

Return of spontaneous circulation (ROSC) is the first step to long-term survival, but is currently only achieved in 40% of OHCA patients.^1^ Furthermore, limiting irreversible ischaemic damage to the brain during ‘no-flow’ and ‘low-flow’ intervals is key to improving neurological outcomes.^3^ Recent UK public health initiatives have focused on education around bystander cardiopulmonary resuscitation (CPR) and provision of public access defibrillators.^4^ However, for OHCA patients these predetermined community factors are no longer modifiable; and once prehospital teams arrive on-scene, treatments follow advanced life support (ALS) algorithms, which have largely remained unchanged for decades.^5^ To improve outcomes in patients with refractory OHCA, novel strategies aimed at increasing the chance of ROSC, whilst preserving cerebral perfusion, should be investigated.

Resuscitative Endovascular Balloon Occlusion of the Aorta (REBOA) provides temporary occlusion of the descending aorta, and is a well-established intervention in trauma patients with torso haemorrhage.^6^, ^7^ Recently, Zone I REBOA (balloon occlusion between the origin of the left subclavian artery and the coeliac axis) has been proposed as an additional treatment for non-traumatic cardiac arrest, by mechanically increasing afterload in order to augment coronary and cerebral perfusion during CPR.^8^, ^9^

During cardiac arrest, antegrade coronary perfusion occurs exclusively in the relaxation phase of chest compression CPR^10^, ^11^, ^12^ This blood flow is driven by the diastolic pressure gradient between the proximal aorta and right atrium, developing a resultant coronary perfusion pressure (CPP).^13^ Multiple preclinical studies have demonstrated that balloon occlusion of the aorta during external chest compressions can augment CPP by increasing aortic diastolic blood pressure (AoDBP); and increase the chances of successfully achieving ROSC.^14^, ^15^, ^16^, ^17^, ^18^ Furthermore, several studies have demonstrated REBOA during CPR increases carotid blood flow and cerebral perfusion pressure,^17^, ^19^, ^20^, ^21^ and that REBOA infers greater carotid blood flow compared to bolus dose epinephrine – potentially avoiding the deleterious effects of epinephrine on cerebral perfusion.^15^, ^21^

### Rationale

Human data concerning the potential role of aortic occlusion in refractory cardiac arrest are mainly comprised of a number of case reports and observational case series.^22^, ^23^, ^24^, ^25^, ^26^, ^27^, ^28^ Therefore, a prospective evaluation of whether REBOA can improve ROSC and neurological outcomes is still required, and several randomised controlled trials of REBOA in OHCA are currently ongoing.^29^, ^30^

At the time of publication, prehospital REBOA is available in one urban UK Helicopter Emergency Medical Service (HEMS) for the management of subdiaphragmatic non-compressible torso haemorrhage.^6^ However, no UK prehospital services currently deploy REBOA in the setting of OHCA. A recent single-centre observational study has demonstrated the feasibility of prehospital REBOA in non-traumatic OHCA in Norway.^9^ However, primarily due to geographical constraints, the mean time (standard deviation) from dispatch to aortic occlusion was 45.6 (±6.3) minutes. REBOA is likely to be a time-critical intervention, and its potential benefits may be more pronounced when applied earlier after the onset of OHCA. The primary objective of this study is to determine the feasibility of prehospital aortic balloon occlusion in adult patient with refractory non-traumatic cardiac arrest in a UK setting.

### Study objectives

The Emergency Resuscitative Endovascular Balloon Occlusion of the Aorta in Out-of-Hospital Cardiac Arrest (ERICA-ARREST) study (ClinicalTrials.gov: NCT06071910) will evaluate the feasibility of deploying REBOA in a UK Helicopter Emergency Medical Service (HEMS). Using compressed geography, and targeted dispatch, alongside a well-established and governed arterial access programme (SPEAR),^31^ the study will assess the feasibility of delivering the intervention in a mixed UK urban and rural setting, within a more rapid timescale. Finally, this study aims to document the detailed physiological response to REBOA during ongoing CPR, using invasive blood pressure (IBP) monitoring, end-tidal CO2 (ETCO2) and measurement of cerebral regional oxygen saturation (rSO2) using near-infrared spectroscopy (NIRS) (See Table 1).

**Table 1 t0005:** Study outcome measures.

**Primary outcome measures**
1. Device delivery [Time frame: within 1 h of initiation]
The proportion of patients where prehospital Zone 1 REBOA for OHCA is achieved, with the balloon inserted to 35–55 cm, proximal arterial blood pressure transduced and evidence of loss of distal invasive blood pressure trace during CPR confirming aortic occlusion.
2. Procedural timings [time frame: within 1 h of initiation]
• Time taken to achieve REBOA for OHCA in minutes
• Time taken from start of the procedure (arterial catheterization) to balloon inflation in minutes
• Total duration of REBOA (inflation to final deflation) in minutes
• Time from arrival at scene to REBOA (balloon inflation) in minutes
• Time from 999 call to REBOA (balloon inflation) in minutes

**Secondary outcome measures**

1. Haemodynamic and oxygenation responses [time frame: within 1 h of initiation]
• Change in aortic diastolic pressure in mmHg
• Change in central venous pressure in mmHg
• Change in calculated coronary perfusion pressure (where cannulated) (CPP) mmHg
These hemodynamic end-points will be presented as a consecutive case series (continuous data plots per patient) and a descriptive summary for the whole cohort of absolute values and change in values between key time intervals: pre-occlusion, during occlusion, post-occlusion.
2. Near infra-red spectrometry [time frame: within 1 h of initiation]
• Change in brain regional oxygen saturation (rSO2) in %
These cerebral oxygenation end-points will be presented as a consecutive case series (continuous data plots per patient) and a descriptive summary for the whole cohort of absolute values and change in values between key time intervals: pre-occlusion, during occlusion, post-occlusion.
3. End Tidal CO2 [time frame: within 1 h of initiation]
• Change in ETCO2 in kPa
These circulatory-surrogate end-points will be presented as a consecutive case series (continuous data plots per patient) and a descriptive summary for the whole cohort of absolute values and change in values between key time intervals: pre-occlusion, during occlusion, post-occlusion.

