**Inclusion criteria**
• Non-traumatic OHCA • 18 to 80 years old • No flow interval known or estimated to be <10 min • In cardiac arrest (with no sustained ROSC) on arrival of the EAAA ERICA-ARREST team

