**Fig. 1 f0005:**
[figure not shown]
**Study flowchart.***Abbreviations*: EAAA: East Anglian Air Ambulance; OHCA: out-of-hospital cardiac arrest; SPEAR: specialist percutaneous emergency aortic resuscitation; SOP: standard operating procedure; RFA: right femoral artery; RFV: right femoral vein; ERICA-ARREST: The Emergency Resuscitative Endovascular Balloon Occlusion of the Aorta in Out-of-Hospital Cardiac Arrest study; REBOA: resuscitative endovascular balloon occlusion of the aorta; ETCO2: end-tidal CO2; RsO2: cerebral regional oxygen saturation; AoDBP: aortic diastolic blood pressure; CVP: central venous pressure; CPR: cardiopulmonary resuscitation; ROSC: return of spontaneous circulation.

Alongside standard ETCO2 and cerebral oximetry monitoring, the proximal and distal arterial pressures will be measured during balloon inflation. The REBOA operator will then inflate the balloon with saline until the distal arterial pressure waveform is lost. Once the balloon is inflated, the REBOA catheter will be secured to prevent migration or dislodgement. If ROSC is achieved without significant instability, the balloon will be gradually deflated by 0.5 ml every 30 s, guided by invasive physiology. Post resuscitation care will follow standard EAAA and Resuscitation Council UK guidelines.^38^ Resuscitation will be terminated if the patient remains in cardiac arrest following standard EAAA protocols; considering the clinical context, patient factors, point-of-care ultrasound findings and blood gas analysis if available.

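### The whole-cohort physiological changes are cut by balloon occlusion, not by CPR, so readings after return of spontaneous circulation (ROSC) mix with the response to REBOA during CPR

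*Protocol article*

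**What the plan says.** The Study objectives section of the protocol article states that "this study aims to document the detailed physiological response to REBOA during ongoing CPR", measured by invasive pressure, ETCO2 and near-infrared spectroscopy, and it refers the reader to Table 1.

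Under secondary outcome measures, Table 1 uses the same presentation rule for haemodynamics, rSO2 and ETCO2. Each has continuous plots per patient and "a descriptive summary for the whole cohort of absolute values and change in values", where the change is the "change in values between key time intervals: pre-occlusion, during occlusion, post-occlusion". The time frame is one hour from initiation and does not stop at ROSC. None of the three intervals carries a condition on CPR or ROSC. By contrast, the device-delivery outcome in the same table does specify that loss of the distal trace is judged during CPR.

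Patients enter in arrest: "In cardiac arrest (with no sustained ROSC) on arrival of the EAAA ERICA-ARREST team". The Intervention section then says: "If ROSC is achieved without significant instability, the balloon will be gradually deflated by 0.5 ml every 30 s". Table 1 counts REBOA duration from inflation to final deflation. Table 3 records aortic diastolic pressure and ETCO2 every 30 s and rSO2 every second, all throughout, and it records the time of sustained ROSC. The Statistical methods section plans descriptive summaries (means or medians as suits the data) and gives no rule on ROSC.

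**The concern.** Diastolic pressure and coronary perfusion pressure under chest compressions are different quantities from the same pressures with a beating heart. The Background makes this point for coronary flow: in arrest it occurs only in the relaxation phase of compressions. If the balloon is still up when the heart restarts, the resulting rise falls inside the during-occlusion interval and is reported as a change with occlusion.

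The study has no control group, so the within-patient contrast is its only evidence on mechanism. The Conclusion says the results will inform the design of efficacy studies. A cohort figure that partly reflects ROSC could be carried forward as the haemodynamic effect of the device.

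**Working it through.** The article gives no figure for these changes, so there is nothing to reproduce. The check has two parts.

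**Which state each interval holds, reading Table 1 as written**

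| Interval | No ROSC under the balloon | ROSC under the balloon |
|---|---|---|
| Pre-occlusion | CPR | CPR |
| During occlusion | CPR | CPR, then spontaneous circulation |
| Post-occlusion | Not described in the article | After ROSC |

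In the right-hand column, the pre-to-during and during-to-post changes each combine a change in balloon state with a change in circulatory state.

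**How much could enter**

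*Readings.* Steps of 0.5 ml per 30 s equal 1 ml per minute. The balloon volume is not given. For an assumed 4 to 20 ml, full deflation takes 4 to 20 minutes. That is 8 to 40 readings of diastolic pressure and ETCO2, and 240 to 1200 of rSO2, per patient with ROSC. Time held at full inflation after ROSC would add to this. The count treats a partly deflated balloon as still occluding, which the interval labels do not settle.

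*Chance that someone is affected.* With n = 20 and a share r of patients gaining ROSC under the balloon, P(at least one) = 1 − (1 − r)^20.
- r = 0.10: 1 − 0.9^20 = 0.88
- r = 0.20: 1 − 0.8^20 = 0.99
- r = 0.40: nearly 1

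The Background gives 40% as the ROSC rate in all out-of-hospital arrests. This trial treats refractory arrest, so 40% serves only as an upper reference; the lower values are assumptions.

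*Shift in a mean pre-to-during change.* If each patient's during-occlusion value is the mean over the interval, the shift is r × w × J. Here w is the share of the interval after ROSC in affected patients, and J is the extra rise at ROSC.

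Assume a CPR-phase rise in diastolic pressure of 10 mmHg and a rise of 40 mmHg once ROSC occurs, so J = 40 − 10 = 30 mmHg, with w = 0.5. The cohort mean change is 10 + r × 0.5 × 30 = 10 + 15r.
- r = 0.10: 10 + 1.5 = 11.5 mmHg, 15% too high
- r = 0.40: 10 + 6 = 16 mmHg, 60% too high

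With w from 0.25 to 0.75 and r from 0.10 to 0.40, r × w runs from 0.025 to 0.30. The shift is then 0.75 to 9 mmHg for J = 30 mmHg. On the same grid it is 0.05 to 0.6 kPa for ETCO2 (assumed J = 2 kPa) and about 0.4 to 4.5 points for rSO2 (assumed J = 15 points). These shifts would appear even with no true effect during CPR.

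*Median.* In the two-value illustration, fewer than half the patients have ROSC for every r up to 0.40, so the cohort median stays at 10 mmHg and the bias is zero. With real spread between patients the median would move somewhat, but less than the mean.

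*After the fix.* If readings are cut at ROSC, w = 0 and the term disappears, whatever r and J are.

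**The case against.** The strongest reply is that Table 1 names three intervals without fixing their limits, and that such detail usually sits in the full protocol (which the article says is available separately) or in the analysis plan. The CPR objective also points to Table 1, so the table could be read under that qualifier. The Abstract states the objective more loosely, as the response to aortic occlusion. For every endpoint the per-patient plots come first, and with at most 20 patients a reader could separate the phases.

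Part of this stands. An unseen document may already restrict the intervals, and the plots would show the problem. But Table 1 is not silent: it commits to a whole-cohort summary with intervals named by occlusion, and following it as written does not deliver the CPR-phase response. The looser objective does not rescue it, since without a control group a rise that comes with the heart restarting is not shown to be a response to occlusion. Nor do the plots correct the cohort figure, which is the number most likely to be quoted.

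A reader might go further in three ways that the article does not support.
- That every haemodynamic change is overstated: for central venous pressure the direction is unclear.
- That post-occlusion values exist almost only in patients with ROSC: the article does not say what happens to the balloon when resuscitation is terminated.
- That the overstatement could exceed 100%: this needs a peak or last value as the per-patient summary, and Table 1 specifies neither.

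**Conclusion.** The point holds as a mismatch between the stated aim and the cohort summary. As written, the during-occlusion value of any patient with ROSC under the balloon includes spontaneous-circulation readings, and that patient's post-occlusion values follow ROSC. The bias is expected to be upward for diastolic pressure, coronary perfusion pressure, rSO2 and ETCO2, on the assumption that these rise when native circulation returns.

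The size cannot be fixed from the article. The 15% to 60% range depends on the assumed rises, ROSC share and window share, and on the use of means; with no ROSC under occlusion the bias is nil.

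It might be inferred that the study's conclusions are at risk. They are not: these are descriptive secondary outcomes, the article ties no test or progression rule to them, and the primary feasibility outcome is untouched. Severity is moderate, and the change is a cheap improvement.

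**What to change.** In Table 1, define the cohort during-occlusion summary as CPR-phase readings only: from inflation to the first of ROSC, start of deflation or termination of resuscitation. Take one summary value per patient before summarising over the cohort, and name it in advance. Report post-ROSC readings with the balloon up, readings during deflation and post-deflation readings separately, each with its own denominator. Keep the per-patient plots and mark ROSC on them.

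The sustained ROSC time is already in Table 3. Transient ROSC is not listed there and would have to be read from the recorded traces, so the definition should say how it is handled. This changes the analysis only; no clinical procedure is affected.

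The cost is some wording in Table 1 and a little more analysis, with no new data. The reported change may look less favourable.

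If the full protocol or analysis plan already contains this restriction, it is enough to bring Table 1 into line with it.

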## Methods

### Study setting

East Anglian Air Ambulance (EAAA) is a UK HEMS organisation that provides prehospital critical care in the East of England in support of the East of England Ambulance Service NHS Trust (EEAST)). The East of England is a geographic area of 20,000 km^2^ and has approximately 6.4 million inhabitants.^32^ Two or three-person HEMS teams, each with at least one physician and critical care paramedic, are dispatched from one of two bases (Cambridge and Norwich) by either helicopter or ground response vehicle, depending on patient location, weather, and time of day.^33^, ^34^ Prehospital consultants are available 24 h a day as part of the HEMS team or on call via telephone for advice.

Each year EAAA is tasked to approximately 3000 primary missions and attends 2000 patients, of which approximately 25% are OHCA. In addition to ALS interventions, the HEMS team can deliver enhanced decision-making and critical care interventions, including point-of-care ultrasonography, arterial blood pressure monitoring, central venous access, targeted vasoactive medications, prehospital emergency anaesthesia, and mechanical ventilation.^5^, ^35^

### Trial design

This is a prospective, single-arm, interventional feasibility study, conforming to Stage 2A of the IDEAL clinical trial guidelines for evaluation of a surgical intervention.^36^ The study is designed to gather information on the feasibility of the intervention, so will not include a control group for comparison. During the study recruitment period, the EAAA team will continue to attend and manage patients in the East of England. In cases of OHCA, alongside standard resuscitation, the HEMS team will identify patients who meet study eligibility criteria (Table 2).

**Table 2 t0010:** Eligibility criteria for the ERICA-ARREST feasibility trial of prehospital Zone I (supra-coeliac) REBOA for refractory non-traumatic OHCA.

**Inclusion criteria**
• Non-traumatic OHCA • 18 to 80 years old • No flow interval known or estimated to be <10 min • In cardiac arrest (with no sustained ROSC) on arrival of the EAAA ERICA-ARREST team
**Exclusion criteria**

• Patients < 18 or > 80 years of age • Known terminal illness • Severe comorbidity/multimorbidity • Inability to deploy mechanical CPR • Pregnancy (obvious or suspected)

*Abbreviations:* REBOA: resuscitative endovascular balloon occlusion of the aorta; OHCA: out-of-hospital cardiac arrest; EAAA: East Anglian Air Ambulance; CPR: cardiopulmonary resuscitation; ROSC: return of spontaneous circulation.

### Intervention

The study intervention is Zone I aortic occlusion using REBOA in patients who remain in cardiac arrest despite standard ALS.

The use of percutaneous, ultrasound-guided femoral arterial and central venous access during ongoing cardiac arrest is already well-established at EAAA. This vascular access programme is termed Specialist Percutaneous Emergency Aortic Resuscitation (SPEAR).^31^ ERICA-ARREST represents an extension of the SPEAR technique, including upsizing of the femoral arterial sheath and insertion of the Zone I REBOA catheter. Delivery of REBOA will only be conducted by teams with ERICA-ARREST-trained senior physicians in prehospital emergency medicine with extensive experience in SPEAR or other endovascular resuscitation techniques.

After arriving at an ongoing resuscitation, the HEMS team will conduct a rapid assessment to understand the circumstances of the arrest; and to ensure that high-quality CPR and ALS are underway. If eligibility criteria are met, the team will proceed to REBOA insertion following a rapid brief to other clinicians present. Both groins will be widely exposed, prepared with 2% chlorhexidine gluconate/70% isopropyl alcohol, and covered with a sterile drape.

Percutaneous cannulation of the femoral artery will be performed under ultrasound guidance. Once the access needle is in the vessel lumen, a flexible guidewire will be inserted, and the position confirmed using a long-axis ultrasound ‘wire-sweep.’ Ultrasound images of needle insertion and the guidewire position will be recorded and stored in a secure online data environment. After the guidewire has been inserted, a 5Fr sheath (MERIT Prelude®, Merit Medical, Utah, USA) will be placed. During the vascular access phase, the operator will also gain femoral venous access using another 5F sheath, which is a standard SPEAR intervention.^31^ Whilst not mandated for the study, it is encouraged as reliable central venous access is desirable for administration of vasoactive medications and enables estimation of CPP.

In eligible ERICA-ARREST patients, the arterial sheath will be upsized to 8Fr (MERIT Prelude®, Merit Medical, Utah, USA) (Fig. 1). After removing the guidewire, the catheter sidearm will be connected to a pressure transducer to verify arterial placement and patency. A pressure-transduced ER-REBOA catheter (Prytime Medical, Boerne, TX, USA) will then be inserted through the 8Fr sheath with an approximate insertion depth of 35–55 cm based on external landmarks (xiphisternum to femoral insertion point), with the aim of placing the balloon in Zone 1.^37^

